### Interventions

To increase consistency between groups, most procedures are the same between the therapeutic DC group and the prophylactic DC group, except the bone flap management. Once the legal surrogate signs consent and confirms randomization, the intervention commences. Before the operation, the best medical treatments will be administered in accordance with the recommendation of the BTF guidelines [33]. For obtaining full course (initial, intra-operative and post-operative) of ICP and CPP variations, ICP monitor will be placed before the craniotomy and kept at least 5 days after surgery. Given the patients with mass lesion often associate with ventricles compression and midline shift, intraparenchymal ICP monitor will be preferred. The probe will be properly placed and fixed in the frontal lobe of lesion side drilling through the designed craniotomy incision without affecting normal procedure.

The unilateral trauma craniotomy model will be adopted, as suggested by Potts et al. [34]. The scalp flap should locate 1 cm beyond the border of the skull window. Craniotomy should reach at least 15 × 12 cm with fully exposed areas, which extended down to the temporal base and curve round the parietal to the side of the midline within 2 cm. After mass lesion evacuation, the dura should be sutured on relaxation and expansion by the temporal fascia or artificial dura. Then, for the prophylactic DC group, the bone flap will be removed. For the therapeutic DC group, the decision of whether or not to replace the bone flap will depend on brain swelling. If the brain tissue protrudes above the base of the temporal skull window, the bone flap will not be replaced.

General care monitoring is aimed to maintain SaO_2_ > 95 %, mean systolic blood pressure > 90 mmHg, temperature < 37 °C and PaCO_2_ 35-40 mmHg. Central venous catheters will be placed in all patients for volume monitoring and resuscitation.

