As per the BTF guideline, a stepwise approach will be preferred to regulate ICP management. Maintaining ICP < 25 mmHg and CPP > 60 mmHg are the target of the critical care treatment. Conventional therapies include head elevation (30°), ventilation, sedation, osmotic dehydration, external ventricular drainage and neuromuscular blockade. The short active propofol (5–100 μg/kg/min) and fentanyl (25–100 μg/h) are used for sedation. Mannitol (1 g/kg) is routine diuretic for osmotherapy. Equiosmolar hypertonic saline (23.4 %, 0.686 ml/kg in bolus) will be considered in patients with refractory intracranial hypertension or rebound phenomenon treated by mannitol. The short half-life of vecuronium (0.2 mg/kg/h) is selected for neuromuscular paralysis agent. Hyperthermia (32 °C–34 °C) will be added to the STBI patients when ICP is refractory even maximal medical treatment.

During critical care, repeated computed tomography (CT) scan will assess intracranial evolution if ICP > 20 mmHg. For craniotomy patients, salvage DC will be performed when there are deterioration of imaging findings (midline shift > 5 mm and/or cisternal compression) and malignant intracranial hypertension (ICP 25–30 mmHg > 1 h or ICP > 30 mmHg, regardless time). For DC patients, even there is no consensus on the optimal time of cranioplasty [35], and systematic review also questioned the definition of “early” which varies from 1 to 4 months [36, 37], it is rational to recommend bone flap replacement as early as 2 months after surgery once their performances achieving the clinical standard.

Scheduled CT scan will be performed at 1, 3, 7, 30 and 180 days after surgery. Additional CT scan will carry out depending on the condition of patient.

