### Follow-up and data collection

After randomization, patients will be assessed at 1 week and 1, 6 and 12 months. Patients who cannot be followed up at seven days will be assessed upon being discharged. For upfront exit patients, their surrogates should mark the previous data whether or not could be used in study. All patient information and imaging findings will be uploaded to a database using the case report form (CRF).

The initial data collection will be assessed at the emergency room by an attending physician. This collection will include baseline status, torso and/or extremities AIS, trauma severity (GCS, motor score and pupillary reaction), CT parameters (mass lesion type, volume of haematoma and midline-shift), time of injury-to-operation, cause of injury and initial laboratory features (arterial blood gas parameters, coagulation and platelet count).

The 1-week follow-up will include intra-operative brain swelling event, salvage craniectomy, laboratory features, early complications and ICP and CPP control. Intra-operative monitoring values will be recorded at the point of probe fixation, dura incision, dura suture and scalp closure. Post-operative ICP control will be recorded as daily ICP burden (number of hrs/d with ICP > 25 mmHg) and total ICP burden (number of days with ICP > 25 mmHg), as well as the same method recording daily and total CPP burden (CPP < 60 mmHg) [38].

At 1, 6 and 12 months follow-up, the independent blinded assessor will face-to-face evaluate intervention outcomes, quality of life, late complications and time of cranioplasty using standard questionnaire. The questionnaire includes the Extended Glasgow Outcome Score (GOSE), EQ-5D. If the discharged patients cannot attend scheduled follow-up, especially at time point of 6 or 12 months, the questionnaire will be sent to the documented permanent address. Only if these methods are invalid, the surrogate will be investigated to finish the questionnaire by telephone.

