### Outcomes

The Primary endpoint is a favorable outcome at 12 months after randomization as measured by GOSE (5–8). The core secondary endpoint is the quality of life indicated by EQ-5D. Further secondary endpoints include mortality and complications at corresponding time point, ICP and CPP control and incidence of salvage DC in craniotomy patients.

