### Blinding

Since the study is conducted at a single center and interventions probably result in different outcomes and qualities of life, ‘ideal blinding’ is not realistic in PRECIS. We use an assessor-blinding method to investigate the study outcome. The independent assessors (IAs) will not be involved in the randomization or intervention. IAs will not be able to obtain the distribution information or the specific treatment procedures using CRF.

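### Recording time of cranioplasty at a face-to-face visit tells the blinded assessor who lost the bone flap, so the GOSE rater is partly unblinded to arm

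*Protocol article*

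**What the plan says.** **Who rates, and how.** Under Follow-up and data collection, at 1, 6 and 12 months "the independent blinded assessor will face-to-face evaluate intervention outcomes, quality of life, late complications and time of cranioplasty using standard questionnaire". GOSE and EQ-5D belong to that questionnaire. Post, and then a telephone call to the surrogate, are used only when the patient does not attend.

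**What is rated.** Under Outcomes: "The Primary endpoint is a favorable outcome at 12 months after randomization as measured by GOSE", with 5–8 counted as favourable. EQ-5D is the core secondary endpoint.

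**What blinding is claimed.** The Abstract and Study design call the trial assessor-blind. The Blinding section concedes that "ideal blinding’ is not realistic in PRECIS", then relies on assessors who take no part in randomization or intervention, and adds that "IAs will not be able to obtain the distribution information or the specific treatment procedures using CRF".

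**How the arms differ.** Under Interventions, the only planned difference is what happens to the bone flap. After evacuation of the lesion, "for the prophylactic DC group, the bone flap will be removed". In the therapeutic arm it depends on swelling: "If the brain tissue protrudes above the base of the temporal skull window, the bone flap will not be replaced". Craniotomy patients may lose the flap later through salvage DC. The opening is large ("Craniotomy should reach at least 15 × 12 cm with fully exposed areas"). For later repair, "it is rational to recommend bone flap replacement as early as 2 months after surgery"; no latest time is given.

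**The concern.** The safeguard under Blinding is that the assessor does not learn which procedure was done. The task given to the assessor under Follow-up discloses it. A cranioplasty time exists only if a flap was taken off, so a date, or the absence of one, shows craniectomy status. It does so at 12 months even when the defect has been closed. Before repair, a face-to-face visit shows the same thing directly.

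Craniectomy status matters because flap management is what the trial compares. The primary endpoint turns on a rater's judgement between GOSE 4 and 5. The trial has one centre, its primary hypothesis favours the therapeutic arm, and the Background says that approach is the centre's existing practice. A rater who can often infer the arm could shift borderline ratings without meaning to, and EQ-5D is collected at the same visit. Whether a patient has died needs no such judgement.

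**Working it through.** **1. The plan's own figure.** The point rests on no stated figure, but the sample size provides the inputs for step 4. With 38% against 54%, 5% two-sided and 80% power, without continuity correction:

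n = [1.96·√(2·0.46·0.54) + 0.842·√(0.38·0.62 + 0.54·0.46)]² / 0.16², which gives 152 per arm.

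Allowing 10% for dropout gives 168 (152 × 1.10) or 169 (152 / 0.90), against the stated 168. The figure reproduces and this point does not affect it.

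**2. What flap status reveals about arm.** Every prophylactic patient treated as allocated has the flap off. Let f be the share of therapeutic-arm patients with the flap off, whether for swelling at the first operation or through salvage DC. Assume equal numbers assessed per arm, and an assessor who guesses prophylactic when the flap was removed and therapeutic when it was not.

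- Flap kept: therapeutic arm with certainty.
- Flap removed: P(prophylactic) = 1/(1 + f).
- Arm guessed correctly overall: 0.5·1 + 0.5·(1 − f) = 1 − f/2. Chance alone gives 50%.

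| f | Correct guess, 1 − f/2 | P(prophylactic, given flap removed) |
|---|---|---|
| 10% | 95% | 91% |
| 1/3 | 83% | 75% |
| 1/2 | 75% | 67% |
| 70% | 65% | 59% |
| 90% | 55% | 53% |

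The article does not state f. One third is borrowed from the retrospective European series in the Background and is only an assumption; the other values show the range.

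**3. The same in patients, at f = 1/3.** Of 168 therapeutic patients, 56 lose the flap and 112 keep it. Those 112 are identified with certainty. The 168 prophylactic patients are also guessed correctly, so 280 of 336 are right, which is 83%.

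**4. Illustration of consequence.** Assume no true difference, 46% favourable in both arms (the midpoint of 38% and 54%), 168 per arm, and a rating shift b in favour of one arm. The documents give no value for b.

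SE = √(2·0.46·0.54/168) = 0.0544

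P(false positive in that direction) = 1 − Φ(1.96 − b/SE)

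- b = 0: 2.5%
- b = 3 points: 8%
- b = 5 points: 1.96 − 0.05/0.0544 = 1.04, so 15%
- b = 8 points: 31%

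With 151 evaluable per arm (168 less 10%), a 5-point shift gives about 14% two-sided, against a nominal 5%.

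**5. How large a 5-point shift is.** Deaths cannot be moved across the 4/5 cut. The Background gives 30–50% mortality for severe TBI in general. If that applied here, moving 5% of an arm would mean misrating 5/70 = 7% to 5/50 = 10% of its survivors, all in one direction. That is possible but not small, so step 4 shows sensitivity and is not a forecast.

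**The case against.** **Flap status is not allocation.** This is the strongest reply, and it stands. A reader might infer that the primary outcome is in effect rated unblinded. The documents do not support that. Therapeutic-arm patients also lose the flap, and the Background calls swelling beyond the skull window common. At f = 90% the assessor is right only 55% of the time. Certainty applies only to patients who kept the flap.

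**The limitation is admitted, and the safeguard is worded narrowly.** The Blinding section says ideal blinding is unrealistic and speaks of what can be learned through the CRF. Hearing about a cranioplasty from the patient is not, strictly, reading it in the CRF. So the two sections conflict in purpose more than in letter. The concession does not settle the matter, because the article then offers assessor blinding as the remedy, and the cranioplasty item undermines it for no need.

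**The visible defect is an argument about early visits.** Many defects may be closed by 12 months, when the primary endpoint is rated. Nor may one say that no flap can be back by 1 month: the 2-month timing is a recommendation. This weakens the visual cue but not the questionnaire item, which discloses the procedure after repair too.

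**Same assessor throughout.** A reader might also infer that one person sees a patient at every visit and carries the knowledge forward. The article does not say so. It refers to assessors in the plural, and rostering may be set out in the full protocol.

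**A standard questionnaire limits discretion.** This is true, and it lowers the plausible size of any shift. It does not remove judgement at the 4/5 boundary.

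**Conclusion.** The concern holds in a limited form. As written, the blinded assessor learns whether each patient had a craniectomy, and so is partly unblinded to arm. The extent is 1 − f/2: from 95% correct at f = 10% to 55% at f = 90%, and 83% if one third of therapeutic-arm patients lose the flap. This rests on patients being treated as allocated, on similar numbers assessed per arm, and on an f that the article does not give.

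The 12-month GOSE cut and EQ-5D are exposed; mortality is not. The rise in one-directional false positives from 2.5% to about 15% depends on an assumed 5-point shift and is an illustration only. Nothing in the documents shows that ratings will be biased, or in which direction. The change is worth making because the exposure is avoidable, touches the primary endpoint and costs little to reduce.

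**What to change.** 1. Take time of cranioplasty off the assessor's questionnaire and have the trial executive team, which already fills the CRFs, record it there.
2. Have the assessor complete GOSE and EQ-5D by structured interview, with the patient's head covered, before any question on complications.
3. Keep late complications with the independent assessor, recorded after GOSE and EQ-5D. Passing them to the executive team would give a secondary endpoint to the unblinded neurosurgeons running the trial.
4. Record the assessor's guess of allocation, so that the degree of unblinding can be reported.
5. Describe the trial as partially assessor-blinded.

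The postal and surrogate-telephone routes should not be counted as blinding measures, since patients and surrogates may know the procedure.

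The cost is a CRF change and a standing instruction for visits. Sample size and treatment are untouched. Blinding remains imperfect: patients may mention their operation, and the complications item can itself reveal it once asked.

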### Outcomes

The Primary endpoint is a favorable outcome at 12 months after randomization as measured by GOSE (5–8). The core secondary endpoint is the quality of life indicated by EQ-5D. Further secondary endpoints include mortality and complications at corresponding time point, ICP and CPP control and incidence of salvage DC in craniotomy patients.

### Statistical analysis

The analysis will be processed on the principle of intention. Patients who drop out or violate initial distribution will be considered as the worst outcome. Considering the probability of craniotomy patients treated by salvage DC, an as-treated analysis will also be implemented, as recommended in two-arm clinic trial [39]. Parametric data will be described by mean and standard deviation. Non-parametric data will be described by median and quartile. Categorical data will be presented using number and percentage.

The primary outcome of the study will be evaluated using the Pearson chi-square test with unadjusted risk ratio and 95 % confidence interval. Adjusted analysis of primary outcome will be assessed using logistic regression for pre-specified factors and any other covariates presenting significant difference between the two groups. The pre-specified subgroups include: age, GCS, pupillary response, mass lesion type and hypotension. Secondary outcome including assessment of quality of life, mortality at 6 and 12 months and incidence of complications will also be assessed using unadjusted analysis and adjusted regression. To investigate the risk factors of postoperative refractory hypertension (salvage DC), univariate and multivariate analysis will be used to identify potential variables of craniotomy patients.

Depending on the results of regression models, the receiver operating curves will be used to evaluate the discrimination. The Hosmer–Lemeshow test will process the goodness-of-fit of models [40]. A P value < 0.05 is considered statistically significant. All statistical analysis will be computed by SPSS software (version 19.0).

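### The worst-outcome rule for drop-outs names no endpoint, so applied as written it counts patients lost while alive as deaths in the mortality endpoint and as having complications

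*Protocol article*

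**What the plan says.** The Statistical analysis section opens with the general statement "The analysis will be processed on the principle of intention". The next sentence is "Patients who drop out or violate initial distribution will be considered as the worst outcome". No endpoint is named, and the sentence stands before the paragraph that separates the primary from the secondary analyses. That paragraph then states that "mortality at 6 and 12 months and incidence of complications will also be assessed using unadjusted analysis and adjusted regression".

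The Outcomes section confirms mortality and complications as endpoints: "Further secondary endpoints include mortality and complications at corresponding time point". No section gives either of them its own rule for drop-outs.

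Follow-up and data collection sets the contact points: "After randomization, patients will be assessed at 1 week and 1, 6 and 12 months". For patients who cannot attend, it adds a postal questionnaire and, as a last resort, a telephone interview with the surrogate. For early exits it says "For upfront exit patients, their surrogates should mark the previous data whether or not could be used in study". The section on adverse events makes death a serious adverse event, to be reported within 24 hours of being recognised.

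**The concern.** For a favourable/unfavourable GOSE endpoint, the worst-outcome rule is a recognisable, if blunt, convention: a drop-out counts as unfavourable. Mortality has only two values, so there the same rule can only mean death. For complications it means that one occurred.

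A patient examined at 6 months and then lost would be entered as dead at 12 months although no death was recorded. Mortality would become a mixture of deaths and losses to follow-up, and the mortality table would show more deaths than the trial's own serious adverse event reports. Any difference in retention between arms would be reported as a difference in mortality.

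The point concerns drop-outs. The same sentence also covers patients who depart from their allocation, which is a separate matter.

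**Working it through.** **Inputs from the article**
- Mortality of severe traumatic brain injury, m: 30 % to 50 % (Background).
- Drop-out margin: 10 % overall, not split by arm (Sample size).
- 168 patients per arm; 5 % two-sided significance level (Sample size).

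**Assumptions**
- The share of survivors lost, d. The article's 10 % refers to all patients, so d = 10 % is a working value.
- Any split of d between arms.
- The Pearson chi-square test, named for the primary endpoint, is also used for unadjusted mortality.

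**The plan's own figure.** With 38 % against 54 % favourable, 80 % power and pooled variance:

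n = [1.96·√(2·0.46·0.54) + 0.8416·√(0.38·0.62 + 0.54·0.46)]² / 0.16² = 151.1, so 152 per arm.

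152 × 1.1 = 167.2, so 168 per arm and 336 in total. The stated sample size reproduces and is not in dispute. The 10 % margin is therefore the plan's working expectation of loss.

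**Inflation with equal loss.** Counted mortality = m + d(1 − m). With d = 0.10:

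| True m | Counted mortality | Survivors counted as dead, per arm |
|---|---|---|
| 30 % | 0.30 + 0.10 × 0.70 = 37 % | 168 × 0.07 = 11.8 |
| 40 % | 0.40 + 0.10 × 0.60 = 46 % | 168 × 0.06 = 10.1 |
| 50 % | 0.50 + 0.10 × 0.50 = 55 % | 168 × 0.05 = 8.4 |

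If the whole 10 % of randomised patients were lost alive, the excess would be 10 points, or 168 × 0.10 = 16.8 patients per arm.

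With the same d in both arms, the difference in counted mortality is (1 − d) times the true difference. If true mortality is equal, no false difference arises.

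**Unequal loss, equal true mortality.** The false difference is (d₂ − d₁)(1 − m). The chance of a significant result is from the two-sided pooled z-test (equivalent to Pearson chi-square) with 168 per arm:

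Φ[(Δ − 1.96·se₀)/se₁] + Φ[(−Δ − 1.96·se₀)/se₁], with se₀ from the pooled proportion and se₁ from the two separate ones.

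| Assumed loss of survivors | True m | Counted mortality | False difference | Chance of p < 0.05 |
|---|---|---|---|---|
| 8 % v 12 % | 30 % | 35.6 % v 38.4 % | 2.8 points | 8.3 % |
| 8 % v 12 % | 50 % | 54.0 % v 56.0 % | 2.0 points | 6.6 % |
| 5 % v 15 % | 30 % | 33.5 % v 40.5 % | 7.0 points | 26 % |
| 5 % v 15 % | 50 % | 52.5 % v 57.5 % | 5.0 points | 15 % |

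Worked example for 5 % v 15 % at m = 30 %: the pooled proportion is 0.37, se₀ = √(2·0.37·0.63/168) = 0.0527, 1.96·se₀ = 0.1033 and se₁ = 0.0525. The first term is Φ[(0.07 − 0.1033)/0.0525] ≈ 0.26 and the second is negligible.

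**Which time point.** A patient seen at 6 months has an observed 6-month status. The distortion therefore falls mainly on 12-month mortality, and reaches 6-month mortality only through patients lost earlier.

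**The case against.** **The rule may be meant for GOSE only.** The article never literally says that lost patients count as deaths, and it mostly uses the word outcome for the favourable/unfavourable endpoint. The authors may have meant only that a drop-out counts as unfavourable, and an analysis plan that is not shown may say so. This stands as a caution about intent. It does not remove the point, because the sentence is a stated rule with no limit, in the section that also analyses mortality and complications. The objection is to what the rule does when followed, not to missing detail.

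**The fallbacks reduce loss.** Postal and telephone contact should recover the vital status of many patients. That lowers d but does not change how a patient who is still lost is counted.

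**The background mortality may not fit.** The 30–50 % is for severe brain injury in general, and the trial's eligibility criteria are narrower. This is true, so the range is illustrative. The excess is d(1 − m), so lower true mortality would make it larger.

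**A stronger reading that the documents do not support.** A reader might infer that the rule biases mortality against the therapeutic arm, because prophylactic-arm survivors return for cranioplasty while patients whose flap was replaced have no such reason. The article says only that "it is rational to recommend bone flap replacement as early as 2 months after surgery", and makes this conditional on clinical status. It does not say that cranioplasty must be done at the trial centre. Some therapeutic-arm patients also lose the flap, through intra-operative swelling or salvage surgery, in a proportion not given. Both arms share the scheduled CT scans, including day 180, and the 1-, 6- and 12-month visits. Differential loss, and its direction, is conjecture.

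**Conclusion.** The point holds as a fault in a stated rule. Applied as written, it counts patients lost while alive as deaths and as having complications. The inflation of mortality needs no assumption about the arms: it is 5 to 7 points at the article's 30–50 % mortality if 10 % of survivors are lost.

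A false difference between arms needs unequal loss. The figures of 2.0–2.8 and 5–7 points show sensitivity under assumed splits and do not forecast the trial's result.

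Mortality is a further secondary endpoint, so the correction is worth making but does not by itself put the primary comparison in doubt.

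**What to change.** 1. State that the worst-outcome rule applies only to the dichotomised 12-month GOSE, with a drop-out counted as unfavourable.
2. Analyse mortality on documented deaths and known vital status, drawing on the scheduled visits, the postal and telephone contact and the serious adverse event reports. Censor patients of unknown status at the date last known alive. Kaplan–Meier estimates at 6 and 12 months would keep the planned time points.
3. Analyse complications as observed up to last contact.
4. Add a sensitivity analysis of the primary endpoint that imputes missing 12-month GOSE from the 1- and 6-month GOSE, where use of earlier data is permitted. The rule kept in step 1 is exposed to unequal loss in the same way, and this shows how much the result depends on it.

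The cost is mainly wording, because the visits, contacts and reports are already planned. The date of last contact must be recorded, and the article does not list it. A surrogate's refusal to let earlier data be used will limit steps 2 to 4 for that patient. Censoring and imputation assume that loss is unrelated to outcome given the observed data. That assumption cannot be verified and should be stated with the results.

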### Sample size

The sample size calculation is on the basis of the variance of outcomes. The favorable outcome of DC in previous studies ranged from 30 % to 61 % [9, 15, 41–43]. Some results may not be applicable because they included patients with diffusion injury and used DC as a secondary therapy. When primary DC treated patients for mass lesions, the favorable outcome of prophylactic DC in 781 patients was 38 % [44–54]. In our centre using therapeutic DC, the favorable outcome of therapeutic DC was 54 % [30]. After including a safety margin of 10 % to account for patients who drop out, we calculate that a sample size of 336 (each arm 168) will be sufficient to reach a significance level of 5 % (two-side) and a power of 80 %. The sample size will be re-assessed and adjusted during interim analysis.

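### Scoring patients treated off-allocation as the worst outcome contradicts the stated intention-to-treat analysis and puts surgical adherence into the primary endpoint.

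*Protocol article*

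**What the plan says.** All of the following is in the Methods of the protocol article.

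- **Principle (Statistical analysis).** "The analysis will be processed on the principle of intention".
- **Scoring rule (the next sentence).** "Patients who drop out or violate initial distribution will be considered as the worst outcome". The article does not say what counts as violating the allocation.
- **Additional analysis (same paragraph).** "Considering the probability of craniotomy patients treated by salvage DC, an as-treated analysis will also be implemented". The groups for this analysis are not defined.
- **Endpoint and test.** Outcomes: "The Primary endpoint is a favorable outcome at 12 months after randomization as measured by GOSE (5–8"). Statistical analysis: "The primary outcome of the study will be evaluated using the Pearson chi-square test with unadjusted risk ratio and 95 % confidence interval".
- **What each arm requires (Interventions).** In the prophylactic arm the flap is always removed. In the other arm, "For the therapeutic DC group, the decision of whether or not to replace the bone flap will depend on brain swelling", and a flap must stay out if brain tissue protrudes above the stated level.
- **Salvage DC (Interventions).** It is a planned step for patients whose flap was replaced, triggered by stated imaging and ICP criteria.

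**The concern.** Under intention to treat, a patient who receives the other operation stays in the allocated arm with the outcome actually observed. The scoring rule keeps the patient in the arm but discards the outcome. A prophylactic-arm patient whose flap was replaced and who reached GOSE 7 would be counted with the failures. The chi-square test would then compare the proportions who did well and were also treated as allocated, which is a different quantity from the stated endpoint.

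If violations are unequal between arms, the test finds a difference when the operations do not differ. If they are equal, a true difference is diluted. Either way the primary result depends partly on how surgeons followed the allocation, and on how someone later decides what a violation is.

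The opportunity to violate is not symmetric. Any replaced flap breaches prophylactic allocation, whereas removal and replacement can both comply in the therapeutic arm. The Background adds that this centre normally reserves primary DC for fulminant swelling, so replacing the flap over a slack brain is its usual practice.

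**Working it through.** **Inputs from the article.** 168 per arm; favourable rates of 38% (prophylactic) and 54% (therapeutic); two-sided 5%; 80% power; 10% margin for dropout.

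**Assumptions, because the article gives no figures.** The violation share per arm is v_T (therapeutic) or v_P (prophylactic). Violators have the average prognosis of their arm. Under no true effect, both arms have 46% favourable, the midpoint (38 + 54)/2.

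**Step 1: the plan's own sample size.** The pooled-variance formula for two proportions is

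n = [1.960 × √(2 × 0.46 × 0.54) + 0.842 × √(0.38 × 0.62 + 0.54 × 0.46)]² / 0.16² = 151.1, so 152 per arm.

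152 × 1.1 = 167.2, so 168 per arm and 336 in all. The stated figure reproduces. The margin is for patients who drop out; nothing is added for violators.

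**Step 2: effect of the scoring rule on the rates.** Analysed rate = true rate × (1 − v). For example, 0.46 × (1 − 0.10) = 0.414, a spurious gap of 4.6 points.

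**Step 3: false-positive chances with no true effect.** Exact binomial enumeration of the two-sided 5% chi-square test, 168 per arm:

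| v_T | v_P | Analysed rates, T v P | Significant for therapeutic | Significant for prophylactic |
|---|---|---|---|---|
| 0 | 0 | 46.0% v 46.0% | 2.8% | 2.8% |
| 0 | 5% | 46.0% v 43.7% | 6.7% | 0.9% |
| 0 | 8% | 46.0% v 42.3% | 10.7% | 0.5% |
| 0 | 10% | 46.0% v 41.4% | 14.1% | 0.3% |
| 5% | 5% | 43.7% v 43.7% | 2.7% | 2.7% |
| 10% | 0 | 41.4% v 46.0% | 0.3% | 14.1% |

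**Step 4: power when 54% v 38% is true (same enumeration).**

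| v_T | v_P | Analysed rates, T v P | Power |
|---|---|---|---|
| 0 | 0 | 54.0% v 38.0% | 85% |
| 10% | 10% | 48.6% v 34.2% | 77% |
| 10% | 0 | 48.6% v 38.0% | 51% |

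**Step 5: the additional as-treated analysis, if salvage cases were moved to the DC side.** This destination is an assumption. Let m be the number moved and q their favourable rate. With no true effect each arm has 0.46 × 168 = 77.28 favourable, and the groups become

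(77.28 − mq)/(168 − m) versus (77.28 + mq)/(168 + m).

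- m = 15% of 112 = 16.8, q = 10%: 75.60/151.2 = 50.0% versus 78.96/184.8 = 42.7%, a gap of 7.3 points.
- Smallest case, m = 10% of 84 = 8.4, q = 30%: 74.76/159.6 = 46.8% versus 79.80/176.4 = 45.2%, a gap of 1.6 points.
- Largest case, m = 25% of 112 = 28, q = 10%: 74.48/140 = 53.2% versus 80.08/196 = 40.9%, a gap of 12.3 points.

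The number of craniotomy patients (84 to 112), the salvage rate (10 to 25%) and q (10 to 30%) are all assumed.

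**The case against.** **Direction.** A reader might infer that the scoring rule biases the trial towards its own hypothesis. The article does not establish this. The therapeutic arm has a binding swelling rule that can also be broken, by replacing a flap despite protrusion or removing one without it. If those breaches, or salvage DC, were counted as violations and were the more common, the bias would run the other way. Equal shares leave no bias under no true effect. This objection stands: the therapeutic direction is plausible and no more. It does not rescue the rule, because an undefined rule that can move the result either way is still a fault in the primary analysis.

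**As-treated analysis.** A reader might also infer that this analysis is a fallback that displaces the randomised comparison, or that it too must favour therapeutic DC. The wording makes it additional, and adding such an analysis is common. The article does not say where salvage cases go, nor where therapeutic-arm patients with primary DC go, so the gaps in Step 5 describe one possible version. What remains is narrower: salvage follows deterioration after randomisation, so regrouping those patients selects on prognosis, and the groups need defining.

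**Dropouts.** Worst-outcome scoring of patients with no outcome is a recognised conservative choice for a binary endpoint. That stands; the fault is in applying it to patients whose outcome is known.

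**Side inferences.** One might read the rule as turning survivors into deaths in the mortality analysis. One might also read it as scoring withdrawn patients as failures when the surrogate refuses use of earlier data, given that "their surrogates should mark the previous data whether or not could be used in study". The article does not say how the rule applies in either case, so neither is claimed here.

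**Conclusion.** The contradiction is in the current text and does not depend on any assumed rate: the plan claims intention to treat and then overwrites known outcomes of patients treated off-allocation. This concerns the primary analysis of the primary endpoint and should be corrected before analysis. A later analysis plan that followed the sentence would carry the fault forward.

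The size is illustrative. Violation in one arm only, at 5 to 10%, raises the chance of a false significant result in the direction that favours the other arm from 2.8% to between 6.7% and 14.1%. Power can fall from 85% to 51% if the violators are in the therapeutic arm, or to 77% with 10% in each arm. These figures rest on assumed violation shares and on violators having average prognosis. The as-treated point is secondary: a false gap of about 2 to 12 points, and only under the assumed inputs and destination of salvage cases.

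**What to change.** 1. Analyse every randomised patient in the allocated arm with the observed 12-month GOSE, whatever operation was done.
2. Limit worst-outcome scoring to patients whose 12-month GOSE is missing.
3. Define an allocation violation for reporting purposes. State that salvage DC performed under the protocol's own criteria is part of the therapeutic strategy and is not a violation.
4. Label the as-treated analysis exploratory and define its groups, including where salvage cases and therapeutic-arm primary DC cases are placed.

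The cost is a few sentences in the analysis section. The 12-month GOSE is already scheduled for all patients and the sample size stays at 336. With all 168 per arm observed, power for 54% versus 38% is about 85%, and the per-direction error returns to 2.8% by exact calculation at 46% favourable (nominal 2.5%).
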